Importantly, VR is reported to consistently stimulate the autonomic nervous system, as evidenced by increases in heart rate (HR) and skin resistance [19]. It can also lead to reduced vagal activity in the parasympathetic system, as shown by lower HR variability [20], indicating a similar mental fatigue state [21]. Research further suggests that engaging with immersive virtual content increases cognitive demand, potentially causing cognitive decline due to the user's limited attentional resource [22]. Despite being a promising technology that engages the specific motor-cognitive processes that are critical for fencing warm-up and competition-related performance, key concerns remain. It is not yet explored to what extent on-field VR combat can prime the real-world performance, nor what the potential effects are on mental fatigue in fencers. Consequently, this study will compare the effects of virtual combat (using VR) with those of traditional warm-up combat in the specialized warm-up section, on fencing-specific performance and fencers' fatigue levels. This study seeks to inform practitioners to evaluate and optimise warm-up practices. It is particularly relevant when access to an appropriate competitive sparring partner may be limited by availability, or an adapted preparation is required in official competitions, in consideration of the fencer's initial fatigue state.

*Aims*. The primary aim is to compare the acute effects of a 10-min VR combat with a 10-min traditional one-on-one combat during the 20-min specialized warm-up section, on subsequent fencing-specific psychomotor performance and subjective mental and physical fatigue levels in fencers. The secondary aims are: (1) to explore the athlete's psychological experience of the task load, readiness, and enjoyment; (2) to explore the behavioral indicators of mental fatigue and physiological response in the two specialized warm-up conditions.

*Hypotheses*. The hypotheses are: (1) VR combat will benefit the fencing-specific psychomotor performance, while inducing less subjective physical and mental fatigue due to the entertaining game nature. (2) Fencers will perceive less task load in a similar HR response, but more readiness and enjoyment after the embedded VR combat than traditional one-on-one combat. (3) The behavioral indicators of mental fatigue will align with the subjective perceptions of fencers.

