#### Virtual reality combat

2.8.1

Two VR headsets (Quest 3, Meta, US) with the same fencing-themed exergames named "Fencing VR: En Garde Arena" (Abstron Pvt Ltd., Pakistan) will be prepared. One VR headset will be equipped with two controllers (held with both hands) for each of the two fencers (see Fig. 3 A and B). The combat area (i.e., piste) will be framed consistently by the researcher. The Epee competition mode and its virtual environment will be selected for standardization. The VC mirrors the official rules and core cognitive demands of real Epee combat, without any physical impact from the avatar and virtual sword. Participants will compete (against VR as in Fig. 3 C and D) individually for 10min, during which the mean value of the HR response (HRmean) will be calculated.

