#### Traditional one-on-one combat

2.8.2

In official competition, pre-competition preparation after the physical activation typically follows a specialized warm-up section including coach-led technical drills (i.e., footwork, distance, lunge, blade exercises) and a phase of one-on-one combat. This simulation involves high-intensity engagements where fencers execute actual sword fighting. In TC, the paired fencers will be asked to maintain the official attacking tempo to score point by point against each other for 10min, as VC, following the FIE (Fédération Internationale d'Escrime) competition rules. The combat will be controlled under strict timing via an electronic scoring apparatus, which is commonly used in daily training and competitions. The HRmean in TC will also be calculated.

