#### Questionnaire

2.9.1

The digital questionnaires will be activated and presented on the tablet at each measurement (i.e., T0, T1, T2). The survey platform (www.wjx.cn) will record the sequence, starting and finishing time automatically. The questions will be answered by reading and sliding the digital scales. The VAS has been validated for fatigue assessments and applied during the real fencing training sessions and competitions for the subjective mental fatigue measures (MVAS) [8]. The participants will slide the marker of the electronic scale to answer "How mentally fatigued do you feel right now?" at T0, T1, and T2. The marker will be initially positioned at "0″ and hidden until participants touch the interface. Two ends of the line will be anchored from "0″ to "100″, indicating "not at all" and "maximum" levels of mental fatigue, respectively. The backend of the online system will record the MVAS by converting it into a 0–100 AU digital form. The digital scale will allow a reset and require confirmation before submission to ensure the value is aligned with the intended response. Meanwhile, after each MVAS measure at T0, T1, and T2, the Rating of Perceived Exertion (RPE) will be measured via the digital CR-10 for subjective physical fatigue [27]. Similarly, at T2, the participants will be further asked to report "readiness to perform" (VAS-Re) and "enjoyment" (VAS-Enj) on VAS following the single-item approach [28], and NASA-TLX (6 subscales on a 21-point Likert scale) based on their experience with the specialized warm-up section. The total estimated completion time for all questionnaires is 1min.

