### Statistical analyses

2.11

Data will be cleaned, analyzed, and visualized in MATLAB_R2023b software. The missing data will be reported and deleted by case. The data will be reported as mean and standard deviation. The significance level will be set at p < 0.05. Linear mixed-effect model (LMM) with fixed-effect factors for time, condition, and their interaction, and a random intercept for ID, will be applied to each performance variable (i.e., RT, RAcc, LT, LAcc) and subjective fatigue variable (i.e., MVAS, RPE). The Shapiro–Wilk test will be conducted to assess the normality of the residuals. Sphericity will be evaluated using Mauchly's test. When appropriate, Bonferroni post-hoc tests will be used. Other subjective perceptions (i.e., VAS-Re, VAS-Enj, NASA-TLX) and HRmean will be compared between conditions via paired sample t-tests. The normality of the difference scores will be verified using the Shapiro–Wilk test. If violated, the non-parametric Wilcoxon signed-rank test will be used instead. For significant effects in LMM, partial eta-squared will be calculated. For t-tests, Cohen's d will be computed. The classification criteria will follow Cohen's convention: for partial eta-squared, 0.01 = small, 0.06 = medium, and 0.14 = large effect; for d, 0.2 = small, 0.5 = medium, 0.8 = large effect.

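### The similar-heart-rate clause of hypothesis 2 cannot be supported by the paired difference test planned for HRmean

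*Protocol article*

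**What the plan says.** The Introduction (Hypotheses) states: "Fencers will perceive less task load in a similar HR response, but more readiness and enjoyment after the embedded VR combat" than after traditional combat. This makes four claims: three directional (task load, readiness, enjoyment) and one of similarity (heart rate).

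Section 2.11 (Statistical analyses) gives all four the same treatment. VAS-Re, VAS-Enj, NASA-TLX "and HRmean will be compared between conditions via paired sample t-tests", with a Wilcoxon signed-rank test if the differences are not normal. On the threshold: "The significance level will be set at p < 0.05". On effect size: "For t-tests, Cohen's d will be computed". The article gives no equivalence margin, equivalence test or interval rule for judging heart rate similar.

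The measurement windows are also fixed. For virtual combat, section 2.8.1 describes 10 minutes of individual combat, "during which the mean value of the HR response (HRmean) will be calculated". Section 2.8.2 says of the traditional combat, also 10 minutes: "The HRmean in TC will also be calculated". Section 2.9.1 has NASA-TLX answered at T2 "based on their experience with the specialized warm-up section". Section 2.4 defines that section as 20 minutes, made up of technical drills and then VC or TC.

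**The concern.** A paired t-test asks whether the mean difference can be distinguished from zero. Rejection would count against similar heart rate. Non-rejection may mean that the conditions are alike, or only that 20 paired differences are too few to separate them.

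The clause carries weight because similar heart rate is the condition under which a lower task load could be read as a property of the VR format rather than of less physical work. The protocol gives reason to expect that workload could differ: section 2.8.1 notes that virtual combat involves no physical impact from the avatar or sword, while section 2.8.2 describes the traditional combat as high-intensity sword fighting. If a real difference in cardiovascular load went undetected and was then described as similar, a lower NASA-TLX score could be credited to VR without justification.

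The windows add a smaller problem. The two measures joined in one sentence of the hypothesis describe different periods, and half of the period rated on NASA-TLX is common to both conditions.

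**Working it through.** **The plan's own figure.** Section 2.3 derives a minimum of 15 participants from partial eta squared 0.12, α = 0.05, power 0.90, correlation 0.5 and ε = 1.
- f = √(0.12/0.88) = 0.369, as stated.
- With one group and m = 4 measurements, λ = n·m·f²/(1−ρ) = 15 × 4 × 0.369² / 0.5 = 16.34. On 3 and 42 degrees of freedom the power is 0.915.

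So 15 reproduces under that layout. Section 2.3 ties the 20 to be recruited to the first hypothesis; heart rate played no part in the sizing.

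**Inputs for the heart-rate check.** From the protocol: n = 20, paired t-test, α = 0.05. Assumed: a two-sided test (sidedness is not stated), a true difference δ of 5 bpm, and an SD of the paired difference of 8, 12 or 16 bpm.

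**Probability of a non-significant result.** The noncentrality is (δ/SD)·√n and the critical value is t(0.975, 19) = 2.093. The 90% CI half-width is 1.729·SD/√20.

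| SD (bpm) | δ/SD | Noncentrality | P(non-significant), n = 20 | 90% CI half-width (bpm) |
|---|---|---|---|---|
| 8 | 0.625 | 2.80 | 0.245 | 3.1 |
| 12 | 0.417 | 1.86 | 0.576 | 4.6 |
| 16 | 0.313 | 1.40 | 0.736 | 6.2 |

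With 15 completers, the protocol's stated minimum, the three probabilities become 0.385, 0.676 and 0.796.

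**Without assuming bpm values.** At n = 20, a true difference of 0.3, 0.5 or 0.6 SD of the paired difference is missed with probability 0.75, 0.44 or 0.28. The difference detectable with 80% power is 0.66 SD, and with 90% power 0.76 SD.

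**What an equivalence rule would deliver.** Two one-sided tests at 0.05, true difference zero, n = 20:

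| Margin (SD of paired difference) | Power |
|---|---|
| 0.3 | 0.01 |
| 0.4 | 0.12 |
| 0.5 | 0.39 |
| 0.6 | 0.65 |
| 0.7 | 0.83 |
| 0.8 | 0.93 |

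For 80% power, a margin of 0.5 SD needs 36 fencers and a margin of 0.7 SD needs 19.

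**Windows.** HRmean covers 10 minutes (the combat). NASA-TLX covers 20 minutes: 10 of drills plus 10 of combat. Section 2.4 describes the drills once, for both conditions, so they should contribute equally to both ratings and the paired difference still reflects VC against TC. How far the drills pull the two ratings together depends on how fencers weight the period, which the protocol cannot tell us.

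**The case against.** Three stronger readings are tempting, and the document does not support them.

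- *All of hypothesis 2 is untestable.* It is not. Three of its four clauses are directional, and a paired difference test suits them.
- *The plan treats p > 0.05 as proof of similarity.* It states no such rule. Means, SDs and Cohen's d are to be reported, and for t-tests d is not restricted to significant results, so the size of a heart-rate difference would be visible. What stands is that nothing in the plan would allow similarity to be concluded.
- *The 20-minute window halves or invalidates the task-load contrast.* Halving would require equal weighting of the two 10-minute parts, which nothing in the document supports; the combat comes immediately before the rating. Any dilution is conservative: it makes lower task load harder to show and cannot create it. The primary aim also places the combat within the 20-minute specialized section, so anchoring the rating there is defensible.

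It can also be said that task load and physiological response fall under secondary aims worded as exploratory, that the bpm figures rest on assumed inputs, and that a margin might sit in an analysis plan not shown. The first limits the importance of the point. The second is right, and is why a range and SD-unit results are given. The third carries less weight, because the article itself names the test for HRmean and that test does not match the hypothesis.

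**Conclusion.** The concern holds for the heart-rate clause and therefore for the joint claim "Fencers will perceive less task load in a similar HR response". The planned test can refute that clause but cannot support it. The logical point needs no assumption about variability. Its size does: with 20 fencers, a true 5 bpm difference would be missed with probability 24% to 74% for an SD of the paired difference from 8 to 16 bpm, taking the test as two-sided.

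The window mismatch is real but secondary. It probably dilutes the task-load contrast and means the two measures do not describe the same period; it does not invalidate the NASA-TLX comparison.

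Because this is one clause of a secondary, exploratory hypothesis, the change is advisable rather than essential to the trial.

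**What to change.** Keep the paired t-test on HRmean and add the 90% confidence interval of the EXP minus CON difference. Fix a margin in bpm, with its rationale, before data collection. Call heart rate similar only if the whole interval lies within that margin, which is equivalent to two one-sided tests at 0.05. Otherwise report the interval and make no similarity claim.

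The effort is one justified margin and one line of analysis. The real cost is that similarity may often not be shown at n = 20: power is about 0.39 for a margin of 0.5 SD of the paired difference and about 0.93 for 0.8 SD. The margin should be chosen for what it means in practice, not for its power. If no margin can be justified, soften the hypothesis to a description of the heart-rate difference with its interval.

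Optionally, anchor the NASA-TLX prompt at T2 to the 10-minute combat just completed, or keep the present wording and state the mismatch whenever task load and HRmean are interpreted together. Re-anchoring takes one line of questionnaire text, must be done before data collection, and means the score no longer describes the whole specialized section.

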## Discussion

3

This study attempts to verify the previously documented advantages of VR technology[14,15] in a real-world competitive fencing context. The feasibility of VR will be explored to replace the human resources that a coach or sparring partner-led, competitive one-on-one combat requires during the pre-competition warm-up. We hypothesize that VR combat could serve as a warm-up for the subsequent fencing performance. Meanwhile, the brief VR combat is supposed to be flexible, self-organized, and entertaining to buffer fatigue perceptions [17].

This study design demonstrates strong novelty and practical relevance. First, the evidence supporting the redesign of the pre-competition warm-up is derived from empirical longitudinal monitoring data in official fencing competitions [8,9]. The VR application of the dual-task paradigm (combined physical and cognitive exercise) is promoted by positive findings from a 5-week brain endurance training intervention among fencers [18]. Furthermore, the structure, content, and timing of the warm-up session have been developed strictly based on empirical investigations in this fencing community. To the authors' knowledge, this is the first time VR will be integrated in a traditional fencing warm-up. By assessing subjective and objective indicators of mental fatigue and fencing-specific performance, this study will effectively bridge the gap between research and on-field fencing practice.

However, this study protocol is risked by several limitations that should be acknowledged. The acute effects of the intervention will not account for dose-related factors such as difficulty or duration of the VR utilization. Further research may be needed to optimize the dose and timing of the exergame. Moreover, the specialized warm-up will be evaluated using a skill test (i.e., FST) rather than in a real competition, which may limit the ecological validity of the findings [30]. Regardless, it provides a step towards a model for the assessment of performance. Despite these acknowledged constraints, the practice-oriented protocol will provide valuable insights into modulating pre-competition warm-up, managing mental fatigue, and enhancing fencing performance in a real-world context.

## Compliance with ethical standards

All authors declare that the study will be conducted in compliance with all ethical standards.

## Ethics approval

The study is approved by the ethics committee of Tsinghua University (THU-01-2026-0021).

## Data availability statement

No data will be available at this stage.

## Declaration of generative AI and AI-assisted technologies in the manuscript preparation process

No generative AI or AI-assisted technologies have been used in the manuscript preparation process.

